## 5. Treatment of subjects

### 5.1 Investigational product: PpIX-TSLT with Comet

The COMET's non-invasive cutaneous mitoPO2 measurements rely on the PpIX-TSLT (protoporphyrin IX-triple state lifetime technique). The PpIX-TSLT technique measures oxygen by oxygen-dependent quenching of delayed fluorescence lifetime of ALA (5-aminolevulinic acid)-induced mitochondrial PpIX. PpIX is the final precursor of haem in the haem biosynthesis pathway and is synthesized in the mitochondria. The conversion of PpIX to haem is the rate-limiting step and therefore causes a weak delayed fluorescence lifetime. Administration of exogenous ALA enhances PpIX to detectable levels and enhances mitochondrial origin of the delayed fluorescence signal. Measurements are based on the detection of time of extinction of red light emitted by the tissue following excitation with green light (figure 2). This technique was first published in 2006. The technique has been tested and calibrated for use in isolated organs and in vivo. The PpIX-TSLT technique is described in detail by Mik (2013).

[figure not shown]

**Figure 2: Detected delayed fluorescence.** A short lifetime corresponds with high intra cellular oxygen concentration and low PO2 values correspond with a long lifetime (Mik, 2013). The lifetime can be translated to an oxygen tension with the help of a calibration

The COMET measurement system is an oxygen availability measurement tool that measures oxygen tension at the mitochondrial level by means of delayed fluorescence of protoporphyrin IX. The COMET monitor is used observationally. It will not be used to treat patients, nor is the information provided by the COMET used to alter patient treatment. The COMET measurement system is a non-invasive measuring system to determine cellular oxygen availability locally in human skin cells with a high concentration of protoporphyrin IX. It is CE marked as a medical device (DEKRA certificate number 2183975CE01, initially issued on 18 April 2016).

In this study, the mitoPO2 of the skin will be measured. Reliable measurements can only take place with sufficient concentrations of protoporphyrin IX in the mitochondria. Therefore, a self-adhesive patch containing 8mg of ALA (Alacare®; Spirig AG, Egerkingen, Switzerland) will be placed on the anterior chest wall for induction of PpIX, for at least 4 hours before the first measurement can take place. To enhance ALA penetration, the skin will be cleaned with alcohol to remove the exposed layers of stratum corneum. Hair, if present, will be shaved. Following at least 4 hours induction of PpIX, the ALA patch will be removed after the outline of the ALA patch is marked.

After placing the skin sensor (COMET Skin Sensor, Photonics Healthcare, the Netherlands), calibration measurements will be made to ensure the quality of the measurements. Thereafter, 5 measurements will be made in the first minute to establish a reliable and stable measurement. Occlusion of the microcirculation will be accomplished via local pressure with the measurement probe, which we use to validate the actual mitoPO2 measurement. After these measurements, mitoPO2 will be measured each minute for 5 minutes to obtain a mean mitoPO2. To ensure that no other variables influence the measurements, measurement characteristics will be logged. In this log, the circumstances in which each measurement is made will be documented. Known intervening variables include, for example, skin temperature, thus skin temperature will be recorded. Other variables recorded in the log will be vasopressor use, dosage of the vasopressor, and nurse actions. Following mitoPO2 measurement, the ALA patch will be re-used to protect the exposed skin for phototoxicity until the next measurement. After completion of the mitoPO2 measurements the exposed skin will be protected from sunlight for 24 hours. An overview of the mitoPO2 measurement is given below.

[figure not shown]

The skin sensor and other parts of the COMET will be cleaned according to cleaning guidelines for medical devices in the intensive care unit. In this case, the COMET will be cleaned with 70% ethanol. In the case of visible dirt, the COMET will be cleaned with water and soap prior to ethanol 70% application.

## 5.2 Use of co-intervention

Due to the risk of phototoxicity, it is important for the skin exposed to the ALA patch to be protected from sunlight during, between, and for 24 hours following measurements.

## 5.3 Escape medication

Should adverse effects take place, the skin would need to be protected from further damage by light exposure. Possible adverse effects include burning sensation of the skin, pruritis, hyperpigmentation, application site erythema, and local pain. Pain killers could be administered, if local pain would persist despite these precautions.

## 6. Investigational product: the COMET

### 6.1 Name and description of medical device

Photonics Healthcare B.V. has developed an innovative non-invasive bedside monitoring system to measure Cellular Oxygen METabolism (the COMET). This device, for the first time, provides insight in the adequacy of oxygen supply and the actual oxygen demand. Available technologies only measure parameters in the blood, where oxygen is transported, but not where it is actually needed. The COMET measures availability and utilization of oxygen where oxygen is utilized: in the tissue cells.

The COMET measurement system consists of three parts:

1. The bedside COMET monitor: has a multi-touch screen that directly, in real time, displays the mitoPO2, the functional parameter of mitochondrial oxygen availability in mmHg. Additionally, signal quality and sensor temperature indication at the time of the most recent oxygen measurement are shown. The user can set the measurement interval and follow the reaction of cellular oxygen to various interventions, or perform a spot-check, a single measurement on a specific part of the skin of the situation at a particular time. A measurement series in a situation where pressure temporarily stops local blood flow can measure oxygen utilization. The device is a standalone unit that can be mounted on a moveable cart or used on a table.
2. The COMET Skin Sensor: is optically and electrically connected with the COMET measurement device. The optical fibers transmit optical signals for tissue excitation and fluorescence detection. The Skin Sensor creates a diverging excitation pulse allowing a superficial optical measurement of the oxygen in the mitochondria of the cells in the epidermis in a circular area of about 5 mm^2. Fluorescence light from the tissue is collected and transmitted via the detection fiber towards the detector system. The sensor also detects ambient light and the temperature inside the sensor.
3. ALA patch and sensor fixation: The dermatologic agent ALA is applied to the patient skin. The sensor is fixated to the site with the help of a patch on which the skin sensor is placed. Simple ALA patches were developed by Photonamic and are marketed for photodynamic therapy, ALA crèmes are available from Galderma, photocure, DUSA and Biofrontera. This set up allows the physician to place the ALA-patch anywhere on the patient's skin and, after four hours, place the sensor to locally determine the mitoPO2 level in the cells of the epidermis, which is then displayed on the monitor. Measurements can be performed every second for several minutes, or every few minutes for a period of 24 hours on the same spot of skin. After that, another location for the patch should be chosen.

### 6.1.1 The measurement specifications

Photonics Healthcare's COMET monitor measures absolute oxygen availability precisely and exactly where it is needed: in the mitochondria of the active cells. This provides doctors with quantitative insight in the availability and consumption of oxygen in their patients' cells and hence the need for a blood transfusion. To determine the oxygen tension in the mitochondria, the COMET measures the lifetime of the triplet state of PpIX, a precursor of haem and hence haemoglobin. The discovery that PpIX exhibits a 'glow-in-the-dark' effect with an oxygen-dependent life time was published in a Nature journal; patents are awarded in Europe and the US and exclusively licensed by Photonics Healthcare. The COMET probes the tissue with very short pulses of green light generated by a diode-pumped solid state laser. This light is brought to the site via an optical fibre. The COMET then observes the decay of the intensity of delayed fluorescence from the red spectrum of light collected from the tissue in the first milliseconds after the flash. Under normal conditions, PpIX is present in very low concentrations due to the presence of a negative feedback loop in which a product of PpIX, haem, acts to inhibit the production of ALA, a substrate for PpIX. This can be overcome by the exogenous administration of ALA, which on its turn leads to higher concentrations of protoporphyrin IX in the mitochondria. ALA patches are already used in and approved for the therapy of benign skin disorders with photodynamic therapy. Its use is safe and provides good treatment results with excellent cosmetic outcome. The 2x2cm large Alacare patches (8mg) were developed by Photonamic and are marketed for the treatment of actinic keratosis, a benign skin disorder, with photodynamic therapy.

The key specifications of the COMET sensor system are:

- Detection range: 0 – 200 mmHg (arterial oxygen tension does not exceed 100 mmHg in normal physiologic situations).
- Tolerance of Monitor: +/- 15%, at least +/- 3 mmHg, for signal quality >75%, which is similar or better than many clinical measurement systems such as cardiac output (+/- 30%), tissue oxygen (+/- 30%) or haemoglobin (+/-20%). Repeatability and stability of the measurement is high and absolute accuracy will improve as more information about the new measurement becomes known but already is higher than for some current parameters used in the clinic (for example cardiac output).
- Time to result: 1 second (for a prepared measurement location, i.e. placement of ALA-patch 4 hours previously to measurement).
- Simple handling (one hour of training is sufficient to train any doctoral student, nurse or doctor)
- All-in-one system, no need for other equipment or control mechanisms.

### 6.1.2 Current stage of development

The COMET measurement system has been developed based upon applicable regulations, standards (Medical device directive 93/42EEC, IEC 60601 rev 3, ISO 13485) and has been tested in preclinical tests and volunteer studies. The key milestones are described below.

The crucial step in the invention is the exploitation of the oxygen dependent optical properties of protoporphyrin IX. Because this substance is made in the mitochondria and can be measured on the skin, the problem of signal location, that has made all earlier attempts to directly measure cellular metabolism unsuccessful, is solved. First publication of the feasibility of the measurements was in 2006 in Nature Methods.

Subsequently the method was tested in vivo on various organs, validated against existing technologies and it was shown that the measurement could be used to measure oxygen consumption i.e., cellular energy turnover in a first human volunteer. Further studies demonstrated that cellular oxygen availability and consumption could safely be measured using ALA patches and COMET prototypes in a study in 30 human volunteers at Erasmus MC in Rotterdam. It was also shown that information from the skin is representative for other parts of the body. From September 2014 until April 2015, Van Diemen et al. measured the increase of cellular oxygen consumption with the COMET prototype in skin of 28 human volunteers after 4 weeks of daily statin use (Simvastatin, a cholesterol lowering drug suspected of modifying mitochondrial function) and its partial reversal by additional intake of ubiquinol (Q10), which contributes to mitochondrial function. Next to the COMET the study also measured phosphocreatine recovery time after muscle exercise in 7-Tesla-31P-MR spectroscopy and mitochondrial membrane potential in white blood cells. The practically perfect correlation of the results in all groups is a strong validation of Photonics Healthcare's measurement against a very expensive and cumbersome technique.

Photonics Healthcare developed the COMET monitor, the first clinical monitor for cellular oxygen and conducted preclinical research with the help of partners, a Eurostars grant and investors.

In patients receiving ALA assisted photodynamic therapy and during neurosurgery oxygen levels were measured with the COMET. These demonstrate that the COMET can be used in patients and measurements are stable.

## 6.2 Summary of known and potential risks and benefits

As described in the summary of product characteristics of Alacare, most known adverse and serious adverse reactions were reported when this product was used in combination with photodynamic therapy. Since patients in our study are exposed to a smaller light dose (1mJ/cm^2) than used in photodynamic therapy (10J/cm^2) and shorter duration of illumination, we expect less severe and less frequent adverse reactions as described in the summary of the product characteristics. Indeed, the study of Harms et al. acknowledges this by reporting minimal adverse reactions in their study with healthy volunteers. Reported adverse reactions of ALA in combination with photodynamic therapy consisted of adverse reactions localised at the treatment site (local reactions) that were attributable to toxic effects of the photodynamic therapy (phototoxicity) in 99%

of patients. During application of Alacare and prior to photodynamic therapy illumination of the treatment site, 33% of patients show local reactions, most frequently pruritus, burning and erythema. During photodynamic therapy illumination, worsening of local reactions, namely erythema, burning and pain were reported most often. The symptoms are usually of mild or moderate severity and require early termination of illumination in 1% of the patients. Cooling of the treated area alleviated these symptoms. After therapy, pruritus, erythema, scabbing and exfoliation are the most frequent local reactions which are likewise mainly mild to moderate and persist for 1 to 2 weeks or occasionally longer. A common (< 10%) adverse reaction not involving the treatment site is headache. The incidence of adverse reactions in patients receiving Alacare plus photodynamic therapy illumination is shown in table 1.

**Table 1: Incidence of adverse reactions in patients receiving Alacare plasters in combination with photodynamic therapy**

**Adverse reactions involving the treatment site (local reactions)**

|                                                          |                               |                                                                                                                      |
|----------------------------------------------------------|-------------------------------|----------------------------------------------------------------------------------------------------------------------|
| General disorders and application site conditions | Very common
≥ 1/10         | Erythema, exfoliation, irritation, pain, pruritus, scabbing                                                          |
|                                                          | Common
≥ 1/100, < 1/10     | Bleeding, desquamation, discharge, discomfort, erosion, hyper/hypopigmentation, oedema, reaction, swelling, vesicles |
|                                                          | Uncommon
≥ 1/1000, < 1/100 | Burn, discolouration, excoriation, inflammation, ulcer                                                               |
| Infections and infestations                       | Common
≥ 1/100, < 1/10     | Pustules                                                                                                             |
|                                                          | Uncommon
≥ 1/1000, < 1/100 | Infection                                                                                                            |

**Adverse reactions not involving the treatment site**

|                                                        |                               |                                    |
|--------------------------------------------------------|-------------------------------|------------------------------------|
| Nervous system disorders                        | Common
≥ 1/100, < 1/10     | Headache                           |
| Infections and Infestations                     | Uncommon
≥ 1/1000, < 1/100 | Pyoderma                           |
| Psychiatric disorders                           | Uncommon
≥ 1/1000, < 1/100 | Emotional distress                 |
| Respiratory, thoracic and mediastinal disorders | Uncommon
≥ 1/1000, < 1/100 | Epistaxis                          |
| Skin and subcutaneous tissue disorders          | Uncommon
≥ 1/1000, < 1/100 | Skin discolouration                |
| Investigations                                  | Uncommon
≥ 1/1000, < 1/100 | Alanine aminotransferase increased |

In a feasibility study of mitoPO2 measurement in 30 healthy volunteers, 45% of the volunteers had mild pruritus and/or erythema on the day of measurement, with only 2 volunteers experiencing transient hyperpigmentation of the skin due to premature exposure of the primed skin to sunlight. No adverse reactions were seen in our INOX ICU-2 pilot study population (P16.303, results not

published yet). Due to the very low light dose ( $2 \text{ mJ/cm}^2$ ) and short duration (1 second) of illumination per measurement (on average 2 minutes per measurement moment) in comparison to conventional photodynamic therapy ( $10 \text{ J/cm}^2$  and a duration of 10 minutes on average), minimal adverse reactions are expected in our study population.

### **6.3 Description and justification of route of administration and dosage**

In the current form, mitoPO2 measurements need administration of ALA to induce enough mitochondrial PpIX for detection of the delayed fluorescence signal. ALA is a precursor in porphyrin synthesis, and its application induces the accumulation of PpIX inside mitochondria. ALA is clinically used in photodynamic diagnosis and therapy of cancer. While systemic administration of ALA in itself is safe, the transient photosensitization of the skin requires patients to limit exposure to (sun) light in the days after treatment. Obviously, this poses constraints to the use of systemically administered ALA in the general population. As an alternative to systemic administration, ALA can be topically applied. Mik et al. have already demonstrated that topical administration of ALA cream to the skin induces oxygen-dependent delayed fluorescence in rats and humans.

### **6.4 Method of administration**

Previous research with this technique has shown that ALA patches are a safe and reliable method to induce PpIX. Therefore, ALA patches are used in this study to enhance PpIX for the mitoPO2 measurements.

### **6.5 Preparation and labelling of medical device**

In accordance with the Dutch 'Kwaliteitswet zorginstellingen', the medical device used for this study has to be controlled for multiple aspects like safety and quality before it can be used in the hospital. This is done by a department in the hospital, called health technology. The COMET has been through this department and has been approved. It received a label of approval from Leiden University Medical Centre.

## 7. Methods

### 7.1 Study procedures

#### 7.1.1 General

The study population will initially consist of healthy volunteers recruited via LUMC notice boards. Subjects will be interviewed prior to participation by a member of the research team, at which time information about the study will be provided and eligibility for participation will be determined based on the inclusion and exclusion criteria. Due to the 'off-label' use of the Alacare patches, specific information pertaining to its current use will be given. A written informed consent will be obtained from all volunteers. Upon inclusion further instructions for ALA-patch application will be provided along with alcohol wipes and 1 ALA-patch.

A self-adhesive ALA-patch will be applied parasternal and a second ALA-patch 3 hours later to rule out influence of the ALA-patch on the measurement variability, while keeping all other possible influencing variables the same. This offset of 3 hours was chosen since an increase in between- and within-subject variability was observed after 3 hours in the INOX ICU-2 pilot study. The course of mitoPO2 measurements will be measured at multiple predefined moments with several overlapping measurements. Subsequently, mitoPO2 measurements will be performed in neurosurgical ICU/MC at multiple predefined moments. This information will be used to further explore the increased variability in the critical care setting where it was first observed.

The study will include patients undergoing elective neurosurgery with postoperative ICU or MC observation and recovery. Patients are typically admitted to the neurosurgical ward 1 day prior to operation. On that day an information leaflet will be given and informed consent will be sought. Patients or their legal representatives will be told that a person can only participate in the study if he/she meets the inclusion criteria. If written informed consent is given, on the day of the operation, the self-adhesive ALA-patch will be placed parasternal in the operating room in the preoperative phase. Three hours after placement of the first ALA-patch, the second offset ALA-patch will be placed either at the ICU/MC or perioperatively in coordination with the anaesthesiology team. This will be done by a member of the research team. The induction time of PpIX is at least 4 hours, therefore the first measurements will be taken postoperatively. MitoPO2 measurements will follow the same schedule used in the volunteer group. After inclusion of a patient meeting the eligibility criteria, each patient will be assigned a unique study number.

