#### 4.4 Sample size calculation

The statistical significance level will be set at the 5% level. The sample size will be calculated to achieve a statistical power of 90%. In the pilot study preceding the INOX ICU 2 study, performed on 20 critically ill patients, the mean within-subject variability at the final timepoint (after 24 hours) was 8.7 mmHg with a standard deviation of 5.67 mmHg. In a stable ICU population, a within-subject variability greater than 4 mmHg will be deemed to be less precise. This is pragmatically chosen based on the initial course of within-subject variability calculated in the first 2 hours of measurements. Therefore, the sample size calculation would be as follows:

$$Z_{\frac{\alpha}{2}} = 1.96 \text{ (two tailed for } p = 0.05\text{)}$$

$$Z_{1-\beta} = 1.28 \text{ (for } \beta = 0.10\text{)}$$

$$\mu = 8.7 \text{ mmHg}$$

$$\mu_0 = 4 \text{ mmHg}$$

$$\sigma = 5.67 \text{ mmHg}$$

$$n = \left( \sigma \frac{Z_{\alpha/2} + Z_{1-\beta}}{\mu - \mu_0} \right)^2 = 15.$$

To allow for an expected 10% dropout rate the corrected sample size will be  $15 \times 1.1 = 17$ . The sample size will therefore be 17 subjects for both groups. The study will first commence in healthy volunteers. The study will continue in neurosurgical patients admitted to the ICU and MC of Leiden University Medical Center postoperatively. In 2018, on average 19 postoperative neurosurgical patients were admitted to the ICU / MC of the LUMC per month. For the period March 2019 – June 2019 (matching the period in which this study is expected to be executed) the average was 17.25 admissions per month. Taking these averages into account, 17 neurosurgical patients has been deemed feasible in the allotted time. Further information on the number of admissions of neurosurgical ICU/MC patients can be found in appendix 4.

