### 8.2 Possible (serious) adverse events and suspected unexpected serious adverse reactions

The ALA patches are already used in and approved for the therapy of benign skin disorders with photodynamic therapy. Its use is safe and provides good treatment results with excellent cosmetic outcome. The 2x2cm large Alacare patches (8mg) were developed by Photonamic and are marketed for the treatment of actinic keratosis, a benign skin disorder, with photodynamic therapy. In dermatology, its use has been investigated. In phototherapy, the treatment effect depends on the production of singlet oxygen by photoactivation of PpIX. Excitation of PpIX induces apoptosis in cells as a result of oxygen-radical formation. In general, this requires illumination with continuous light and a high cumulative light dose (10 J/cm^2). In contrast, PpIX-TSLT uses short-pulsed excitation and a total light dosage, i.e., orders of magnitude less than used for photodynamic therapy (1 mJ/cm^2). A recent systematic review showed no significant (serious) adverse effects of ALA patches.

Side effects of ALA described with photodynamic therapy are burning of the skin (<50%, resolved in 1-4 days), burning sensation of the skin (<92%), pruritus, hyperpigmentation (22-36%), edematous lesion (35%), application site erythema (92-99%), local pain (1-92%, <30% severe), application site irritation (72%), local haemorrhage(1-4%), and headache (<10%). Most of these reactions resolved within 2 weeks. There are no reported (serious) adverse events. Since the light load at the cutaneous-PpIX-TSLT is much lower than in phototherapy, no adverse events are expected. While PpIX-TSLT is likely to be safe, the effects of phototoxicity after PpIX induction should always be considered a potential risk requiring a risk and safety assessment in any intended application.

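### The 3-hour patch offset does not hold earlier measurement constant: at all four overlaps the older patch has also had one or two more sessions, so the planned tests cannot separate patch age from repeated measurement

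*Protocol*

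**What the plan says.** Section 7.1.1 (General) gives the purpose of the second patch, placed three hours after the first: "to rule out influence of the ALA-patch on the measurement variability, while keeping all other possible influencing variables the same". Sections 2.1 and 4.1 say that the volunteers are there to explore the effect of time since patch application. Section 9.1 names that effect within the primary outcome.

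Section 7.2.1 and its Table 2 fix the sessions. Patch 1 is measured at 0, 1, 3, 6, 24 and 27 hours after the 4-hour induction, and patch 2 at 0, 1, 3, 21 and 24 hours. Section 5.1 describes a session: the patch comes off, the sensor is placed and calibrated, five readings are taken in the first minute, the probe is pressed on the skin to occlude flow, and five further readings follow at one per minute. Afterwards "the ALA patch will be re-used to protect the exposed skin for phototoxicity until the next measurement".

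Section 9.3 plans one inferential comparison: a paired t-test, or a signed-rank test, between the patches at their overlapping moments.

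**The concern.** A two-patch design isolates patch age only if the patches differ in age and nothing else that could affect the readings. Here the older patch has also been lifted, measured and put back more often. If earlier sessions disturb later readings, whether by handling, by light or by pressure, the disturbance would appear in the results as an effect of time since application.

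This matters because the study exists to explain why variability rose late in the pilot. In Appendix 1, Table 1 the rise to 7.3 and 8.7 mmHg came at the seventh and eighth of eight listed moments, so lateness and repetition were already mixed there. The new schedule repeats that ambiguity, while section 7.1.1 says that it has been removed. The parent study would handle a loss of precision with patch age differently from one caused by repeated measurement.

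**Working it through.** **Inputs.** Session times are from Table 2 in section 7.2.1, session content from section 5.1 and the planned test from section 9.3. The printed sample size reproduces: (5.67 × (1.96 + 1.28) / 4.7)² = 15.28, printed as 15, and 15 × 1.1 = 16.5, giving 17. Nothing below depends on it.

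**Step 1: count earlier sessions at each age** (hours after the 4-hour induction).

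| Age (h) | 0 | 1 | 3 | 6 | 21 | 24 | 27 |
|---|---|---|---|---|---|---|---|
| Patch 1, earlier sessions | 0 | 1 | 2 | 3 | – | 4 | 5 |
| Patch 2, earlier sessions | 0 | 1 | 2 | – | 3 | 4 | – |

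At each shared age (0, 1, 3 and 24 h) the count is the same on both patches. Age therefore determines the count. With age as a factor the 11 sessions have rank 7, and adding session count as a second factor leaves the rank at 7. A session effect at fixed age cannot be estimated.

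**Step 2: the same-clock overlaps.** Clock time on patch 2 is its age plus 3 h.

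| Clock (h after patch 1 T0) | Patch 1: age, earlier sessions | Patch 2: age, earlier sessions | Extra age (h) | Extra sessions |
|---|---|---|---|---|
| 3 | 3 h, 2 | 0 h, 0 | 3 | 2 |
| 6 | 6 h, 3 | 3 h, 2 | 3 | 1 |
| 24 | 24 h, 4 | 21 h, 3 | 3 | 1 |
| 27 | 27 h, 5 | 24 h, 4 | 3 | 1 |

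Each paired test mixes three hours of age with one or two sessions. Had overlap meant equal age instead of equal clock time, neither age nor count would differ between the patches, and the two would still not be separated.

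**Step 3: look for an exception.** There is one. Patch 1 at T3 (6 h) and patch 2 at T4 (21 h) both have three earlier sessions, with ages 21 − 6 = 15 h apart. They are on different sites and at clock times 24 − 6 = 18 h apart, so they are not an overlap and section 9.3 does not use them. Time since the last session also differs: 6 − 3 = 3 h on patch 1 and 21 − 3 = 18 h on patch 2.

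**Step 4: what is certain to accumulate.** Section 5.1 makes removal and re-application certain. Repeated light and pressure at one point is not certain. Section 6.1 says that the sensor reads "in a circular area of about 5 mm"² (square millimetres), and section 6.1.1 gives a 2 × 2 cm patch, so one reading covers 5 / 400 = 1.25% of the outline. Section 5.1 has the outline marked but gives no instruction to return to one point.

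**The case against.** **No effect is shown.** No part of the protocol demonstrates that earlier sessions alter later readings. A reader might infer photobleaching from section 8.2, where "the treatment effect depends on the production of singlet oxygen by photoactivation of PpIX", but that sentence concerns photodynamic therapy at 10 J/cm². Taking section 6.2's higher figure of 2 mJ/cm² for every flash, and at least 10 readings per session, four earlier sessions at one point would give 40 × 2 = 80 mJ/cm², or 0.8% of that dose. The method reads lifetime and not intensity (section 12a), and signal quality is recorded and reported. In the pilot, within-subject SD was 3.6 mmHg at 120 minutes, after five earlier listed moments, against 3.0 at the first. This counts against a simple cumulative effect, although the next two moments rose. All of it stands, and it limits the point to what the design cannot separate.

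**Same spot.** A reader might conclude that by T5 each measured point has had at least 40 flashes and four occlusions. The protocol does not support that. Its phrase "for a period of 24 hours on the same spot of skin" describes what the device can do and is not a study instruction. The figure showing the measurement is not available in the text read here.

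**Not fully locked.** A within-patch rank correlation of 1.00 is automatic on any site measured repeatedly and shows nothing. The uneven spacing does carry information: patch 1 gains three sessions in the first 6 h and one over the next 18 h. Across all 11 sessions the Pearson correlation is 0.91. Using this requires an assumed shape for the age effect, and it gives up the same-clock control that the second patch was meant to provide.

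**Descriptive aim.** The study speaks of exploration, and the Summary can be read as promising only the same person at the same time. That is fair, and nothing commits the sponsor to a claim that patches lose precision with age. Section 7.1.1 is nevertheless worded more broadly than that.

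**Conclusion.** The point holds in a limited form. Under the nominal schedule each patch age has exactly one number of earlier sessions, and at four of four overlaps the patch that is 3 h older has also had one or two more. The claim in section 7.1.1 that everything else is kept the same is therefore not true of this design. A carry-over effect, if there is one, could not be told apart from time since application in the planned paired tests.

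This rests on sessions being held at the times in Table 2 and on overlap meaning the same clock time. It is tightest in volunteers. In patients the induction is at least 4 h and patch 1 T0 follows surgery, so true age at a session can vary.

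A reader might infer that repeated measurement explains the pilot finding, or that the study's results would be invalid. Neither follows: the documents do not show such an effect, and the SDs per time point remain valid descriptions. What is limited is the attribution of a change to patch age.

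**What to change.** 1. In section 7.1.1, replace the statement that all other variables are the same. Say that the offset holds subject and clock time constant but not the number of earlier sessions, and limit the conclusion to *time since application including repeated measurement*. Cost: one or two sentences.

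2. In section 9.3, add a descriptive paired contrast of within-subject SD and signal quality for patch 1 T3 (6 h) against patch 2 T4 (21 h), both after three earlier sessions. State that clock time (18 h apart), patch site and time since the last session differ. Cost: analysis text only, since the data are already collected.

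3. Optional, in volunteers at T5: take one further short series at a position inside the same marked outline that is known not to have been measured before, and compare it, paired, with the usual position. This requires the sensor position to be recorded at every session. It tests only flashes and pressure, because the fresh position has shared all the patch lifting; equal SDs would not by themselves establish age as the cause. Cost: a short non-invasive series, slightly more light exposure and an amendment.
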